## Methods

2

### Trial design

2.1

This will be a non-random control trail with single center experience. Elderly patients will be included from the Affiliated Hospital of Southwest Medical University. We developed this protocol based on the 2013 statement of standardized protocol interventions: recommendations for intervention trials (SPIRIT).^[10]^Figure 1 shows the schedule for registration, assessment, intervention, and follow-up in accordance with spirit guidelines.

**Figure 1 F1:**
[figure not shown]
Study period (

 stands for positive).

### Patient population and eligibility criteria

2.2

Inclusion criteria:

(1)all meet the relevant diagnostic criteria for colorectal cancer;(2)all confirmed by electronic colonoscopy and pathological examination;(3)age ≥ 65 years old;(4)consciousness and mental state are normal;(5)operations are all laparoscopic, and all meet the indications of laparoscopic surgery;

Exclusion criteria:

(1)patients with mental disorders such as severe cognitive impairment;(2)patients with severe organ diseases who cannot perform laparoscopic surgery;(3)patients with intestinal obstruction and unable to withstand surgery;

Flow chart is shown in Figure 2.

**Figure 2 F2:**
[figure not shown]
Flow chart (

 stands for the next step).

### Intervention

2.3

The case group will receive ERAS:

a.the first guidance: to explain the disease knowledge of patients, simply understand the stoma care methods, without detailed guidance of stoma care methods;b.preoperative preparation: no intestinal preparation was needed;c.intraoperative intervention: the abdominal cavity was washed with warm water to avoid hypothermiad.follow up guidance: the intervention staff only need to conduct telephone follow-up 1 month after discharge to understand the status of patients.

The control group will receive routine treatment and nursing.

a.First guidance: nurses face the patients on admission, one-to-one through oral and written guidanceThe patients understood the disease-related knowledge, stoma nursing methods, and matters needing attention in daily life;b.Preoperative preparation: according to clinical routine operation, assist patients to improve intestinal preparation;c.Intraoperative intervention: according to the traditional process, there is no need for heating intervention and other measures;d.follow up guidance: the intervention personnel kept in touch with the research subjects during the trial, and 1 month after discharge. Telephone follow-up was conducted to understand the nursing ability and quality of life of patients.

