The surgical team has developed and implemented multidisciplinary care programs, included ERAS, which improves patient outcomes and reduces hospital stay.^[6,7]^ ERAS includes evidence-based changes in traditional care, such as consultation before admission, avoiding mechanical bowel preparation, shortening fasting, carbohydrate drinks for 2 hours before surgery, avoiding fluid overload, minimally invasive surgery, avoiding early removal of drainage tubes, and catheters, and multimodality of opioid retention analgesia, early feeding and activities. In 1 meta-analysis, ERAS during colorectal surgery was significantly associated with the reduction of postoperative complications, total hospital costs, and early recovery of gastrointestinal function, without increasing 30 day readmission or mortality.^[8]^ Another study showed satisfactory short-term clinical results and demonstrated that laparoscopic D2 lymphadenectomy combined with era is safe and feasible.^[7]^ ERAS is widely accepted to be the gold standard for the treatment of colorectal disease in patients.^[8,9]^ However, there are few articles on the elderly. Our study intends to analyze the effectiveness and safety of clinical application of ERAS in elderly patients with colorectal cancer, and to observe its impact on postoperative recovery of elderly patients with colorectal cancer.

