### Postoperative complications

2.6

A medical specialist, the outcome assessor, will be instructed about diagnostic criteria in this study for specific postoperative complications. All participants will be evaluated by the outcome assessor until 30 days after surgery. And we will use evidence-based process of comprehensive geriatric assessment (CGA)^[11]^ to evaluate an older patient's general condition and the risk of adverse outcomes

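### Section 2.3 gives the ERAS arm thinner stoma guidance and less described follow-up contact than control, against its own other items and the Introduction's account of ERAS; items a and d may be transposed

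*Protocol article*

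**What the plan says.** Section 2.3 (Intervention) of the protocol article sets out items a to d for each arm.

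- **ERAS arm.** The first guidance is "to explain the disease knowledge of patients, simply understand the stoma care methods, without detailed guidance of stoma care methods". For item b the text reads "preoperative preparation: no intestinal preparation was needed". Item c is abdominal lavage with warm water. For item d, "the intervention staff only need to conduct telephone follow-up 1 month after discharge to understand the status of patients".
- **Control arm.** On admission, nurses give one-to-one oral and written guidance covering the disease, stoma care and daily life. Bowel preparation follows clinical routine, and no warming is used. For item d, "the intervention personnel kept in touch with the research subjects during the trial, and 1 month after discharge"; the text adds "Telephone follow-up was conducted to understand the nursing ability and quality of life of patients".

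The Introduction describes ERAS as evidence-based changes to traditional care, "such as consultation before admission, avoiding mechanical bowel preparation, shortening fasting, carbohydrate drinks for 2 hours before surgery, avoiding fluid overload", and goes on to minimally invasive surgery, drains and catheters, multimodal analgesia, and early feeding and activity.

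On complications, Section 2.6 says: "All participants will be evaluated by the outcome assessor until 30 days after surgery". Section 2.5 says the same of the specialist.

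**The concern.** The trial sets out to show that ERAS improves recovery over routine care. Two of the four items that define its arms nevertheless give the ERAS patients less than the controls. The limiting words in the ERAS list (guidance that is not detailed, staff who need only telephone) are what one would expect in the description of a comparator.

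This affects what the comparison estimates. If sites follow the text, the ERAS arm differs from control in two ways that favour enhanced care and two that oppose it, and every patient in an arm receives all four. If the text is a transposition, the published description misstates what each arm receives, and a reader cannot tell what was tested. Neither problem can be repaired in the analysis.

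**Working it through.** The plan gives no figure to reproduce on this point. The check sets the texts side by side.

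**Step 1. The four items in Section 2.3.**

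| Item | ERAS arm | Control arm | Arm with more enhanced care, as written |
|---|---|---|---|
| a. First guidance | Disease explained; stoma care in simple form only | One-to-one, oral and written; disease, stoma care, daily life | Control |
| b. Preoperative | No bowel preparation | Routine bowel preparation | ERAS, by the Introduction's account |
| c. Intraoperative | Warm lavage | No warming | ERAS, by the stated purpose of avoiding hypothermia |
| d. Follow-up | One call, 1 month after discharge, on patient status | Contact during the trial and 1 month after discharge; call on nursing ability and quality of life | Control |

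Two items run one way and two the other, within one section.

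**Step 2. Section 2.3 against the Introduction.** Counting drains and catheters separately, and feeding and activity separately, the Introduction names about 11 elements: pre-admission consultation, no bowel preparation, shortened fasting, carbohydrate drinks, avoiding fluid overload, minimally invasive surgery, drains, catheters, multimodal analgesia, early feeding and early activity.

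- Stated in Section 2.3 as differing between arms: 1 (no bowel preparation).
- Applying to both arms through eligibility (Section 2.2 requires laparoscopic surgery): 1.
- Not in Section 2.3: 11 − 1 − 1 = 9. The ERAS first guidance is not counted as pre-admission consultation, because the text does not place it before admission and it is thinner than the control arm's.

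Warm lavage is not in the Introduction's list. Sections 2.4 and 2.7 collect pain relief, first fluid intake, first meal, and gastric tube and catheter times. Section 2.3 describes no analgesia, feeding or tube element that would be expected to move them.

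**Step 3. What the contrast would estimate.** As written:

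ERAS − control = effect of (no bowel preparation + warm lavage) + effect of (less guidance + less contact) + any interaction.

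Only the sum is observed. A null result could be two effects cancelling, and a difference could come from either part. The anxiety score in Section 2.4 is an example of a measure that guidance and contact might plausibly move.

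**Step 4. Contact and the 30-day complication window (secondary).** If discharge is on postoperative day L and one month is taken as 30 days, the call falls on day L + 30. For any L of 1 or more this is later than day 30, in both arms. The scheduled call therefore cannot serve as the day-30 assessment in either arm. Sections 2.5 and 2.6 do not say by what contact a discharged patient is assessed up to day 30, and the only post-discharge contacts described are those in item d, which differ by arm.

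**The case against.** **This is a condensed article.** The Introduction describes ERAS in general, as background, and the full pathway may stand in a protocol that is not shown. The study-period figure is also not shown. This objection stands for the nine omitted elements: taken alone, they would not be a finding. It does not reach items a and d, which are written out explicitly for each arm and contradict the direction of items b and c.

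**The reversal may be intended.** The documents do not settle whether a and d were exchanged, so the point is a request to confirm and not an assertion that they were.

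**A reader might infer that complication ascertainment is unequal and biased toward ERAS.** The documents do not support that. Sections 2.5 and 2.6 state one specialist assessor and one 30-day window for everyone. The item d calls are labelled follow-up guidance and are nowhere named as the route for detecting complications. Contact during the trial may refer to the hospital stay, in which case the post-discharge schedule is one call in each arm. The timing of that call is the same in both arms and cannot by itself create a difference. If a and d are transposed, any excess of contact moves to the ERAS arm, so no direction of bias can be stated. What survives is a risk: patients in more frequent contact with staff may have more opportunity to report a problem.

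**A reader might also infer that an outcome is lost because only the control call covers quality of life.** Quality of life is not among the data items in Section 2.4, the outcomes in Section 2.7 or the primary outcomes named in the Discussion. No planned comparison depends on it.

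**Conclusion.** The point holds in this form. Section 2.3 contradicts itself: two of its four items move the ERAS arm toward enhanced care and two give it less guidance and less described contact than control. It is also at odds with the Introduction, since only one of about 11 named elements is shown as differing between arms. Followed as written, the trial could not attribute a difference, or the lack of one, to ERAS as the Introduction describes it.

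The conclusion rests on the literal text of the a-to-d lists. It does not depend on how long patients stay or on any complication rate. The documents give nothing from which to compute a numerical bias, and none is claimed. First exhaust, first meal and length of stay are in-hospital outcomes that post-discharge calls do not affect.

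Unequal reporting of post-discharge complications is a secondary risk only, resting on an unstated contact route up to day 30 and on one reading of the control arm's item d.

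**What to change.** 1. Reconcile Section 2.3 with the Introduction and confirm which arm items a and d belong to. If further ERAS elements are delivered under a fuller protocol, say so in Section 2.3 and refer to it. The content of care in each arm is for the clinical team to decide.
2. In Sections 2.5 and 2.6, state that complications are ascertained in both arms by the same scripted contact at day 30 counted from surgery, made by or for the outcome assessor and kept separate from the item d guidance calls.

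The first change costs protocol text only. The second is also text if the 30-day evaluation already promised is made by such a contact; if it is not, it adds one short contact per patient.

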### Data collection

2.4

We will collect the relevant indicators based on the final outcomes. The research assistant will collect the following data:

Basic information:

Age, gender, education level, body mass index, pathological type, and stage of cancer, ASA score of anesthesia, preoperative albumin, and globulin level.

Stress response indicators: Fasting blood glucose, C-reactive protein (CRP)

Immune function index: T lymphocyte subsets (CD3 +, CD4 +, CD8 +, CD4 + / CD8 +) and immunoglobulin (IgG, IgM, IGA)

Psychological assessment: Zung's self-rating Anxiety Scale (SAS) was used to evaluate the anxiety of the 2 groups

Postoperative recovery index and Economics: Anal exhaust time, first fluid intake time, total hospitalization time, total hospitalization expenses, gastric tube indwelling time and urinary catheter indwelling time

Postoperative complications: Anastomotic leakage, intestinal obstruction, pulmonary infection, urinary tract infection, urinary retention, wound infection.

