**Methods::**

This is a single center, non-random, parallel-controlled clinical trial, 60 patients aged ≥65 years will be randomized for Case group ERAS and Control group (routine care).

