### Statistical analysis

2.11

In this study, the sample size was estimated by comparing 2 independent samples. Considering the loss of follow-up, the sample size was increased by 10%, so the final sample size (N1 + N2) ∗ (1 + 10%) was 110. Therefore, 55 patients in the case group and 55 patients in the control were selected in this study. SPSS 22.0 statistical software was used for data entry and statistical analysis (*P* < .05 was statistically significant). Statistical description was used for general data, ANOVA of repeated measurement was used for quantitative data, and rank sum test was used for rank data.

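### Tumour site and type of resection are not among the listed baseline data, and the unadjusted tests named would not remove a colon-to-rectum imbalance between non-random groups

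*Protocol article*

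**What the plan says.** **Who is eligible.** Section 2.2 requires that patients "all meet the relevant diagnostic criteria for colorectal cancer" and that "operations are all laparoscopic, and all meet the indications of laparoscopic surgery". The surgical approach is fixed. Tumour site and type of resection are not.

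**How groups are formed.** Section 2.1 states: "This will be a non-random control trail with single center experience". The abstract's Background agrees. The abstract's Methods sentence calls the trial non-random too, yet continues "60 patients aged ≥65 years will be randomized for Case group ERAS and Control group (routine care". Section 2.11 gives a different number: "55 patients in the case group and 55 patients in the control were selected in this study". The article states no matching, stratification or allocation rule.

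**What is recorded.** Section 2.4 introduces its list with "The research assistant will collect the following data". The baseline items are "Age, gender, education level, body mass index, pathological type, and stage of cancer, ASA score of anesthesia, preoperative albumin, and globulin level". The complications are "Anastomotic leakage, intestinal obstruction, pulmonary infection, urinary tract infection, urinary retention, wound infection". The same section lists hospital stay, expenses and urinary catheter time. Tumour site, resection and stoma formation appear neither there nor elsewhere in the article, although section 2.3 covers stoma care in both groups.

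**How it is analysed.** Section 2.11 names repeated-measures ANOVA for quantitative data and the rank sum test for ranked data, and mentions no covariates. The Discussion calls length of stay and complications primary, and promises an analysis of risk factors for complications without naming any.

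**The concern.** In a non-random comparison, a prognostic factor that differs between groups passes straight into the estimated effect unless the design or the analysis handles it. Rectal surgery is pelvic surgery, so site plausibly affects much of what this trial measures: leakage, urinary retention and infection, catheter time, stay and cost. The Introduction itself stresses how many rectal cancer patients there are in China, so a mixed population is to be expected.

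The listed covariates do not stand in for site. A colonic and a rectal patient can be identical in age, stage, ASA score, body mass index and albumin, and pathological type is histology. If one group held more rectal operations, the unadjusted tests would attribute the consequences to the care programme. The planned look at risk factors for complications would also lack an obvious candidate.

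**Working it through.** **The plan's own figure.** Section 2.11 gives (N1 + N2) × 1.10 = 110, so N1 + N2 = 110 / 1.10 = 100, and 55 per group after inflation. The step is arithmetically right. The base of 100 cannot be reproduced, because no effect size, SD, rate or power is given. The point here does not depend on it, except that 55 is used as the group size.

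**Assumptions.** The documents give no rectal shares and no site effects, so these are assumed:
- no true ERAS effect, 55 per group, two-sided 5% test, normal approximation;
- g, the rectum-minus-colon difference in within-site SDs, from 0.25 to 1.0;
- rectal shares p1 and p2 of 40% v 50%, 40% v 60% and 30% v 70%.

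**Formulas.**
- False difference: b = g × (p2 − p1).
- SD including the site mixture: s = √(1 + g² × [p1(1 − p1) + p2(1 − p2)] / 2).
- Standard error: SE = s × √(2/55).
- False-positive rate: Φ(b/SE − 1.96) + Φ(−b/SE − 1.96).

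**Example** (20-point gap, g = 1): b = 0.20; s = √(1 + 0.24) = 1.114; SE = 1.114 × 0.1907 = 0.212; b/SE = 0.94; rate = Φ(−1.02) + Φ(−2.90) = 15.6%.

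| Gap in rectal share | b, in SD (g = 0.25 to 1.0) | False-positive rate |
|---|---|---|
| 10 points | 0.025 to 0.10 | 5.2% to 7.6% |
| 20 points | 0.05 to 0.20 | 5.8% to 15.6% |
| 40 points | 0.10 to 0.40 | 8.2% to 47.9% |

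**Scale.** With 50 analysable per group, the difference detectable with 80% power is (1.96 + 0.84) × √(2/50) = 0.56 SD. The largest false difference in the table is 0.40 / 0.56, or about 70% of that.

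**Complications.** Assume rates of 15% after colonic and 35% after rectal surgery. Shares of 30% v 70% give 0.15 × 0.7 + 0.35 × 0.3 = 21% against 0.15 × 0.3 + 0.35 × 0.7 = 29%, a false difference of 8 points. Shares of 40% v 60% give 23% against 27%, or 4 points.

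**If allocation were in fact random.** With an assumed 50% rectal share, the SD of the difference in share is √(0.25 × 2/55) = 0.095 at 55 per group, so a gap of 20 points or more has probability of about 4%. At 30 per group, the abstract's total of 60, the SD is 0.129.

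**The case against.** The strongest reply is that section 2.4 is not the whole data set. Pain relief is a reported outcome but is absent from it, as are most of the laboratory values of section 2.5 and the geriatric assessment of section 2.6. The schedule and flow chart are not shown, and an article need not reproduce its case report form. This stands. A reader might infer that site will go unrecorded and that an imbalance could be neither seen nor corrected, but the documents do not support that. Colonoscopy is an entry requirement, every patient has an operation at the single centre, and site can be recovered from those records. What remains is that an explicit list, detailed enough to include education level and globulin, names two tumour descriptors but not this one, and that the analysis described would not use it.

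Second, the abstract also says patients are randomised. If they were, imbalance would arise by chance only, and the nominal error rate already allows for that. This stands as a condition. The article calls the trial non-random in three places, and the contradiction has to be settled first.

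Third, the magnitude is assumed throughout, and nothing in the article links site to group. This also stands. A reader could reach a false-positive rate of about 52% by taking a 4-day site difference, an SD of 4 days, a 40-point gap and 50 per group, and leaving out between-site variance. With that variance the SD is √(16 + 16 × 0.21) = 4.4, the SE is 4.4 × √(2/50) = 0.88, and the rate falls to about 44%. Even that is an extreme corner of the range.

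Fourth, site is one confounder among several. True, but most of the obvious others are already on the list.

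**Conclusion.** The point holds in a limited form. As written, the plan compares non-random groups that may contain any mix of colonic and rectal resections, does not list site or resection among its data, and names only tests that take no account of them. Stay, catheter time, expenses and complications are therefore open to confounding by site.

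The size depends on assumptions. At a 10-point gap in rectal share the effect is small (about 5-8% false positives). It becomes material at 20 points if the site effect is large (up to about 16%) and serious at 40 points (up to about 48%). The bias could favour either group, so nothing here shows that the trial would lean towards ERAS. If the groups turn out to be randomised, the argument reduces to chance imbalance. The change is worth making because it is cheap and shows which of these situations applies.

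**What to change.** - **Section 2.4:** add tumour site (colon or rectum), resection performed and stoma formation, taken from the existing colonoscopy and operation records.
- **Section 2.11:** make the main between-group comparisons of stay, catheter time, expenses and overall complications adjusted for site together with the baseline covariates already collected, by linear or logistic regression. Where a rank method is preferred, name a site-stratified one such as the van Elteren test, because the plain rank sum test takes no covariate. The stratified test handles site only, not the other covariates.
- Adjust for site, which is known before surgery. Resection and stoma are settled at operation and are better described by group.
- Report individual rare complications by site descriptively only.
- **Abstract and sections 2.1 and 2.11:** reconcile random with non-random allocation, and 60 with 110 patients. Frequency matching on site is optional and cannot be judged until the way groups are formed is stated.

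**Cost:** a few fields from existing records and somewhat more analysis, with no extra patients or procedures. With about 50 per group, events such as leakage or retention may be too few to adjust for.

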### Study outcomes

2.7

The degree of pain relief, the length of the first exhaustion, the time of the first meal, the length of hospitalization, and the incidence of complications would report.

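### Bowel recovery is recorded as anal exhaust time although stoma patients are expected, and with non-random allocation and no stoma or operation data listed, operation mix could pass for an ERAS effect

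*Protocol article*

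**What the plan says.** All references are to the protocol article.

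- **Population (section 2.2).** The disease criterion is "all meet the relevant diagnostic criteria for colorectal cancer" and the procedure criterion is "operations are all laparoscopic, and all meet the indications of laparoscopic surgery". No tumour site is specified, no anastomosis is required and no stoma is excluded.
- **Intervention (section 2.3).** The first guidance in the ERAS arm is to "simply understand the stoma care methods, without detailed guidance of stoma care methods". In the control arm it covers "stoma nursing methods, and matters needing attention in daily life". Both arms therefore anticipate stomas.
- **Bowel recovery (sections 2.4 and 2.7).** The data list has "Anal exhaust time, first fluid intake time, total hospitalization time". The outcome section names "the length of the first exhaustion, the time of the first meal" and does not repeat the word anal. The Discussion lists the same outcomes in a sentence that calls them primary.
- **Complications (sections 2.4 and 2.6).** The list begins "Postoperative complications: Anastomotic leakage, intestinal obstruction, pulmonary infection" and has six components. All participants are assessed to 30 days. No denominator is stated for leakage.
- **Baseline (section 2.4).** The list starts "Age, gender, education level, body mass index, pathological type, and stage of cancer" and continues to ASA score, albumin and globulin. Tumour site, operation performed, anastomosis and stoma are not on it.
- **Allocation and analysis (sections 2.1 and 2.11).** The trial is described as non-random. The analysis paragraph mentions no stratification or adjustment by procedure.

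**The concern.** Time to first gas per anus does not exist for a patient with an end stoma, and in a patient with a diverting stoma it need not measure the return of bowel function. Staff must then leave the field blank, wait for a late anal event, or enter the time of first gas through the stoma. The text does not say which.

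Each choice ties the result to the number of stoma patients in an arm. Randomisation would limit the difference in that number; non-random allocation does not. The listed data would neither show an imbalance nor allow adjustment for it. First exhaust is one of the five outcomes in section 2.7, so a headline comparison is exposed.

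Leakage has a related but smaller problem: a patient without an anastomosis cannot have a leak. The two measures have different at-risk groups. Leakage needs an anastomosis; anal exhaust needs bowel continuity to the anus. A diverting stoma above an anastomosis disturbs the second and not the first.

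**Working it through.** **1. The plan's own figure.** Section 2.11 gives 110 patients, 55 per arm, after a 10% increase. 110 / 1.10 = 100, or 50 per arm before the increase. The 100 cannot be reproduced, because no effect size, SD, event rate or power is given. (The Abstract gives 60 patients; that is a separate matter, and section 2.11 is used here.)

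**2. Assumptions.** The document gives no stoma share *s*, no share without an anastomosis and no leak rate. All values of these below are assumed and serve only to show scale. Tests are taken as two-sided at 5%, with a normal approximation.

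**3. First exhaust left blank in stoma patients.** Evaluable patients per arm are n = 50 × (1 − s), with the same *s* in both arms. Power ≈ Φ(d√(n/2) − 1.96). Take d = 0.56, the standardised difference that gives 80% power at 50 per arm.

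| s | n per arm | Power |
|---|---|---|
| 0% | 50 | 80% |
| 10% | 45 | 76% |
| 20% | 40 | 71% |
| 30% | 35 | 65% |
| 50% | 25 | 51% |

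This is an upper limit on the loss, since some patients with a diverting stoma do pass gas per anus.

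**4. First exhaust recorded, but shifted in stoma patients.** The shift may come from gas through the stoma or from late anal gas. Let it be D standard deviations. With no true ERAS effect, the bias in the mean difference is D × (difference in stoma share). At 50 per arm the standard error is √(2/50) = 0.2 SD.

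- D = 1, 20-point difference: bias 0.2 SD; rejection probability Φ(1.0 − 1.96) + Φ(−1.0 − 1.96) ≈ 17% instead of 5%.
- D = 0.5, 20-point difference: bias 0.1 SD; about 8%.
- D = 1, 10-point difference: bias 0.1 SD; about 8%.
- Equal shares: no bias.

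**5. How easily shares differ.** With random allocation, 55 per arm and a true share of 30% in both arms, simulation gives about a 25% chance of a difference of 10 points or more, and about 3% of 20 points or more. Non-random allocation sets no such limit.

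**6. Leakage.** Let *r* be the leak rate among patients with an anastomosis, equal in both arms, and *u* the share without one. With all patients as denominator the rate is r × (1 − u).

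- r = 8%, u = 20% v 40%: 8% × 0.80 = 6.4% v 8% × 0.60 = 4.8%. The gap is 1.6 points, or 55 × 0.016 ≈ 0.9 of a patient per arm.
- r = 10%, u = 10% v 30%: 9.0% v 7.0%, ratio 1.29.
- r = 10%, u = 30% v 10%: 7.0% v 9.0%, ratio 0.78.
- r = 10%, u = 20% in both: 8.0% v 8.0%, ratio 1.00; the rate is diluted but the comparison is not biased.

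Among patients with an anastomosis the ratio is 1.00 in every case.

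**The case against.** The strongest reply is that a journal article condenses a fuller protocol. How flatus is recorded in stoma patients, and which denominator serves one complication, would normally sit there or in an analysis plan. Section 2.7 says only first exhaust, and in translated English anal exhaust may simply mean first flatus. Confounding by operation mix also follows from non-random allocation and would touch length of stay and first meal as well.

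Much of this stands. Leakage is one of six components and not a named outcome, and all operated patients are a normal denominator for overall complications. The document does not say that patients without an anastomosis are counted as leak-free, although a reader might infer it from the assessment of all participants.

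Two other strong readings are tempting. One is that the fault cannot be repaired later. But operation, anastomosis and stoma would normally be in the operation note of this single-centre study and could be retrieved; only the route of first gas really needs prospective recording. The other is that a large, known number of patients has no valid exhaust time. The guidance in section 2.3 shows that stomas are anticipated, not how many patients will have one, and not every stoma patient lacks an anal event or an anastomosis.

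The reply does not remove the mismatch itself. The only wording that says how bowel recovery is measured specifies the anal route, and the stated population includes patients for whom that route may be closed. This is a stated measure that does not fit the stated population, rather than an omitted detail.

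**Conclusion.** The point holds in a limited form and should be fixed; it does not invalidate the trial. As written, first exhaust is undefined or open to inconsistent recording in stoma patients. Under non-random allocation, with no operative variables listed, operation mix alone could move it. Leakage is affected less, and its ratio is unbiased if the shares without an anastomosis are equal.

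The size cannot be computed from the document. Under the assumed values, the effect on first exhaust ranges from no bias (equal shares) to a false-positive rate of about 17% (1 SD shift, 20-point imbalance), or a fall in power from 80% to 71% at a 20% stoma share if the values are missing. The leakage example with r = 8% amounts to less than one patient per arm. The conclusion rests on the inference that stoma patients will be enrolled, which sections 2.2 and 2.3 support strongly without stating it.

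**What to change.** 1. In sections 2.4 and 2.7, define the outcome as time from the end of surgery to first passage of gas per anus or via the stoma, and record the route at the bedside.
2. Add four fields to the section 2.4 list, taken from the operation note: tumour site, operation performed, anastomosis (yes/no) and stoma (none/diverting/end).
3. Compare first exhaust stratified by, or adjusted for, stoma status.
4. Report leakage also among patients with an anastomosis, and keep all patients as the denominator for overall complications.

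The cost is four extra fields, one reworded definition and a smaller denominator for the leakage rate. Item 1 should be settled before data collection, because the route of first gas may not be recoverable from records; the other items can be completed later if need be.
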